### Methods

**Study design:** This is an ecological study based on surveillance data from Australia and NZ

**Data collection:** We will collect IPD case notification data from national surveillance institutes (National Notifiable Diseases Surveillance System (NNDSS), EpiSurv) and merge those with census data that will be derived from Australian Bureau of Statistics and Statistics New Zealand. In NZ, all laboratories contribute to the surveillance system.

IPD is defined as a laboratory confirmed infections of *S. pneumoniae* if isolated from a normally sterile site or detected with nucleic acid testing from a sterile site. To be able to compare cases between Australia and NZ, cases detected from a newer generation *S. pneumoniae* antigen test on cerebrospinal fluid or pleural fluid will be excluded (NZ only). (17, 18)

National coverage of childhood immunisation data will be extracted from the National Immunisation registers in NZ and Australia. Fully immunised was defined as eligible children who have completed all of their age-appropriate immunisations by the time they turned the milestone age.

**Sample size:** This is a descriptive study so a power calculation is not required. Preliminary data show us that in 2019 overall IPD rates per 100,000 for Australia and New Zealand are on average 8.4 (95%CI 8.1-8.8), and 9.9 (95%CI 9.1-10.8), respectively. Therefore, this study will provide estimates for IPD rates with sufficient certainty.

**Data analysis:** First, we will compare overall IPD rates per 100,000 and the proportion of cases with serotype 19A between Australia and New Zealand between 2017-2021. Second, we will perform a stratified analysis for ethnicity: Indigenous (Aboriginal and Torres strait islander) versus non-Indigenous for Australia, and Māori and Pacific vs other for New Zealand. Next, we will analyse of IPD rates and serotype 19A rates in different age groups. Furthermore, we will explore whether differences in IPD rates can be explained by differences in national immunisation coverage for pneumococcal vaccinations. In a sensitivity analysis, we will repeat all the analyses only including non-Indigenous children in Australia because Indigenous children receive additional doses of PCV in certain regions (Appendix 1). Cases with missing indigenous status were counted as non-indigenous.

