## Impact

Epidemiological and surveillance studies such as our project, are crucial to evaluate vaccine strategies and to inform public health organizations on vaccine policies to improve health outcomes. This research will provide insight in differences of IPD and serotype rates and the influence of the PCV10 and PCV13 programmes. This study will provide us with an opportunity to compare PCV10 and PCV13 programmes based on real-life data. In addition, we will evaluate the IPD rate in specific ethnic groups who suffer from health inequalities. In these groups, it is even more essential to evaluate the effect of current vaccine strategies. Also, this project will provide essential data on the future decision of vaccine programmes in New Zealand and Australia.

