## Relevance to Māori health

Indigenous populations in New Zealand and Australia, along with Pacific peoples have a much higher burden of disease for IPD.(2, 3, 19) For instance, two-thirds of all IPD cases in 2020 among children aged <5 years were children of Māori (39%) or Pacific (28%) ethnicity.(10) Australia provides two additional PCV23 (Pneumovax 23) doses for Aboriginal and Torres Strait Islander children, from 4 years of age.(7) New Zealand's programme, however, does not have additional doses for Māori or Pacific people. In this study, we will evaluate the IPD rate in specific ethnic groups including Māori as it is even more essential to evaluate the effect of current vaccine strategies in groups at higher-risk for IPD. This study has the potential to guide future decisions regarding vaccine strategies for Māori.

Māori consultation will be requested following the procedure by the Otago university.

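### The sensitivity analysis removes the high-burden Indigenous group from Australia only, which biases the New Zealand/Australia IPD rate ratio upward independently of vaccine programme

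*Protocol*

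**What the plan says.** In Methods, Data analysis, the protocol plans overall IPD rates and the proportion of serotype 19A by country, then a stratified analysis by ethnicity, then rates by age group. The strata are Indigenous versus non-Indigenous for Australia and "Māori and Pacific vs other for New Zealand".

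The sensitivity analysis follows: "In a sensitivity analysis, we will repeat all the analyses only including non-Indigenous children in Australia because Indigenous children receive additional doses of PCV". The sentence goes on to limit this to some regions and points to Appendix 1. The next sentence adds: "Cases with missing indigenous status were counted as non-indigenous". No restriction on New Zealand is stated for the sensitivity analysis.

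The section Relevance to Māori health describes the groups concerned: "Indigenous populations in New Zealand and Australia, along with Pacific peoples have a much higher burden of disease for IPD". For New Zealand it reports that "two-thirds of all IPD cases in 2020 among children aged <5 years were children of Māori (39%) or Pacific (28%) ethnicity". It also notes: "New Zealand's programme, however, does not have additional doses for Māori or Pacific people".

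The Impact section gives the use to which the comparison will be put: "This study will provide us with an opportunity to compare PCV10 and PCV13 programmes based on real-life data".

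**The concern.** The restriction is meant to remove a schedule difference, namely the additional PCV doses given to some Indigenous children in Australia. It does so by dropping a group whose baseline IPD burden, on the protocol's own account, is much higher than that of other Australians. The New Zealand groups described in the same terms remain. The comparison becomes Australia without its high-burden group against New Zealand with its high-burden groups.

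The direction also sits badly with the purpose. If the additional doses prevent disease, they lower the Australian rate, and taking away their influence should raise it. Dropping a high-burden group lowers it instead.

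A ratio that rises, or stays above 1, in this analysis could be read as showing that the main result is robust to the dose difference. Part of that ratio would only reflect who was left out. The study is intended to inform vaccine programme decisions, so the misreading matters.

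**Working it through.** **The plan's own figures.** The protocol gives no size for the effect of this restriction, so there is nothing to reproduce on that point. The one between-country contrast available comes from the 2019 rates: "in 2019 overall IPD rates per 100,000 for Australia and New Zealand are on average 8.4 (95%CI 8.1-8.8), and 9.9 (95%CI 9.1-10.8), respectively". Their ratio is 9.9 / 8.4 = 1.18. That ratio is for overall rates in 2019 and is not a benchmark for the under-5 figures below.

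**Inputs from the protocol**
- Māori and Pacific share of New Zealand under-5 IPD cases in 2020: 39% + 28% = 67%, leaving 33% in other children.
- High-burden groups exist in both countries; no rate ratio is given.

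**Assumptions (not in the protocol)**
- q, the Māori and Pacific share of New Zealand under-5s: 0.30 to 0.45.
- p, the Indigenous share of the Australian population: 0.03 to 0.08.
- RR, the rate ratio of the high-burden group to the rest: taken as the value the New Zealand figures imply, and applied to Australia as well.
- For the null case, equal stratum-specific rates in the two countries and no vaccine difference.

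**Step 1: implied RR in New Zealand.** RR = (0.67/q) / (0.33/(1-q)). At q = 0.30 this is 2.233 / 0.471 = 4.74. At q = 0.45 it is 1.489 / 0.600 = 2.48.

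**Step 2: what the Australia-only restriction adds.** The overall Australian rate is the non-Indigenous rate times 1 + p(RR-1). Restricting to non-Indigenous people divides the Australian rate by that factor, so it multiplies the New Zealand/Australia ratio by it.
- Lowest: 1 + 0.03 × (2.48 - 1) = 1.04.
- Highest: 1 + 0.08 × (4.74 - 1) = 1.30.

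**Step 3: the total in the restricted comparison under the null.** If non-Indigenous Australian children and other New Zealand children have the same rate, the expected ratio is New Zealand overall / New Zealand other = (1-q)/0.33. At q = 0.30 that is 0.70/0.33 = 2.12; at q = 0.45 it is 0.55/0.33 = 1.67.

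**Step 4: how much is already in the unrestricted comparison.** Divide the Step 3 total by the Step 2 factor.

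| q | RR | Total, restricted | Factor added (p = 0.03; 0.08) | Unrestricted (p = 0.03; 0.08) |
|---|---|---|---|---|
| 0.30 | 4.74 | 2.12 | 1.11; 1.30 | 1.91; 1.63 |
| 0.35 | 3.77 | 1.97 | 1.08; 1.22 | 1.82; 1.61 |
| 0.40 | 3.05 | 1.82 | 1.06; 1.16 | 1.71; 1.56 |
| 0.45 | 2.48 | 1.67 | 1.04; 1.12 | 1.60; 1.49 |

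Under these assumptions the unrestricted null ratio is already about 1.5 to 1.9, and the one-sided restriction raises it by a further 4% to 30%.

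**Step 5: the matched restriction.** Non-Indigenous Australia against non-Māori, non-Pacific New Zealand has an expected ratio of 1.00 under the same null.

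Counting cases with missing Indigenous status as non-Indigenous leaves some Indigenous cases in the restricted Australian numerator, which offsets the shift somewhat. The protocol gives no figure for missingness.

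**The case against.** The strongest defence is that the asymmetry has a stated reason. The check targets a schedule difference that exists in Australia and has no New Zealand counterpart, since New Zealand gives Māori and Pacific people no additional doses. It was never offered as a control for baseline risk. That explains why Australia is restricted. It does not remove the imbalance in risk that the restriction creates.

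A second defence is that the planned strata already yield both non-Indigenous Australian and other New Zealand rates, so the like-for-like contrast is within reach. This stands in part: the data will be there. But the protocol does not name that pairing as the sensitivity comparison, and the repeated overall and age-group comparisons remain unmatched.

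Several stronger readings are tempting and are not supported:
- A reader might attribute the whole 1.7 to 2.1 to this analysis. Most of it comes from New Zealand's ethnic mix and is already in the unrestricted comparison.
- A reader might infer that the restriction adds more bias than it removes. The protocol gives no figure for the effect of the additional doses, so the two cannot be ranked.
- A reader might infer that New Zealand will show the higher rate regardless of vaccine. The shift is an upward bias, not a guaranteed result.
- A reader might say that the bias favours the study hypothesis. None is stated: the objective is neutral, and the study calls itself descriptive.
- A reader might set the under-5 figure against the 2019 ratio of 1.18. The two differ in age range and year.
- A reader might take the sentence to compare Australian children with New Zealanders of all ages, or to require an Indigenous stratification within non-Indigenous data. Loose drafting is the likelier explanation of both.

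**Conclusion.** The point holds for IPD rates. As written, the sensitivity analysis biases the New Zealand/Australia rate ratio upward, independently of vaccine programme, because it removes a high-burden group from one country only. The direction follows from the protocol's own description of burden and holds for any rate ratio above 1.

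The size rests on assumptions. The added factor depends on p and on carrying the New Zealand under-5 rate ratio over to Australia. The under-5 total depends on q and on a case share from the single year 2020. The serotype 19A proportion is a share of cases, and a difference in baseline incidence alone does not move it, so the same direction cannot be claimed there.

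**What to change.** Add the matching restriction in Methods, Data analysis: the sensitivity analysis compares non-Indigenous Australia with non-Māori, non-Pacific New Zealand, in the same age bands and calendar years. State that any conclusion about robustness rests on this matched comparison. The Australia-only restriction need not be dropped; if it is also shown, say beside it that it is not matched on baseline risk.

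The cost is about one sentence and a little extra analysis, using strata already planned. The drawback is smaller New Zealand counts in the restricted set. On the 2020 figures only about 33% of under-5 cases would remain, so those intervals will be wider.

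### The sensitivity analysis drops the higher-risk ethnic group from Australia only, so for IPD rates it raises the NZ:Australia ratio through risk mix and cannot isolate the vaccine programme

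*Protocol*

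**What the plan says.** The Data analysis paragraph of the protocol's Methods plans an overall comparison of the two countries, then an ethnic stratification: "Indigenous (Aboriginal and Torres strait islander) versus non-Indigenous for Australia, and Māori and Pacific vs other for New Zealand". Age groups and immunisation coverage follow. The sensitivity analysis comes last: "we will repeat all the analyses only including non-Indigenous children in Australia because Indigenous children receive additional doses of PCV in certain regions". No counterpart is given for New Zealand. The next sentence adds a coding rule: "Cases with missing indigenous status were counted as non-indigenous".

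The section Relevance to Māori health gives the background risk: "Indigenous populations in New Zealand and Australia, along with Pacific peoples have a much higher burden of disease for IPD", and "two-thirds of all IPD cases in 2020 among children aged <5 years were children of Māori (39%) or Pacific (28%) ethnicity". It also says that New Zealand's programme "does not have additional doses for Māori or Pacific people".

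**The concern.** The purpose of the repeat is clear. If extra PCV doses in some Indigenous Australian children hold down the Australian rate, removing those children should show how much of the between-country difference is due to them. But the removal changes two things together: exposure to extra doses, and baseline risk on the Australian side. By the protocol's own statement the removed group still carries the higher burden, so taking it out lowers the Australian rate. New Zealand keeps its own higher-burden groups.

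A check on whether extra doses flatter Australia should be able to weaken an apparent Australian advantage. For IPD rates this one tends to enlarge it. The Impact section says the study will compare the PCV10 and PCV13 programmes and inform later vaccine decisions, so a larger New Zealand excess in the repeat could be taken as support for one programme.

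**Working it through.** **Inputs from the protocol**
- 2019 overall (not child-specific) IPD rates per 100,000 for Australia and New Zealand: "are on average 8.4 (95%CI 8.1-8.8), and 9.9 (95%CI 9.1-10.8), respectively" (Methods, Sample size).
- Higher IPD burden in Indigenous populations of both countries and in Pacific peoples (Relevance to Māori health).
- Māori and Pacific share of New Zealand under-5 cases in 2020: 39% + 28% = 67%, leaving 33%.

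**Assumed, because the protocol does not give them**
- p, the Indigenous share of Australian children: 3–8%.
- r, the Indigenous to non-Indigenous rate ratio in Australia: 2–6.
- q, the Māori plus Pacific share of New Zealand under-5s: 25–45%.

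**1. The protocol's own figures.** The ratio is 9.9/8.4 = 1.18. The implied event counts, (2×1.96/ln(upper/lower))², are about 2,240 for Australia and 524 for New Zealand. Poisson limits on these counts are 8.06–8.76 and 9.07–10.79, which agree with the stated intervals. The standard error of the log ratio is √(1/2240 + 1/524) = 0.0485, so the 95% interval for the ratio is about 1.07–1.30. This is a consistency check only, and the child-based factors below are not applied to this all-age ratio.

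**2. Effect of restricting Australia alone.** The total Australian rate is the non-Indigenous rate × (1 − p + pr). The non-Indigenous rate is therefore the total rate / [1 + p(r−1)], and the NZ:Australia ratio is multiplied by 1 + p(r−1).

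| p | r | factor |
|---|---|---|
| 3% | 2 | 1.03 |
| 6% | 2 | 1.06 |
| 6% | 4 | 1.18 |
| 7% | 6 | 1.35 |
| 8% | 6 | 1.40 |

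Here r is the rate ratio as observed, so it already contains whatever the extra doses achieve. The direction needs only r above 1.

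**3. A scenario with no vaccine effect.** Give both countries identical rates within each stratum, with p of 3–6%, q of 25–45% and r of 2–4.
- Unrestricted ratio, [1+q(r−1)]/[1+p(r−1)]: 1.18 (p=6%, q=25%, r=2) to 2.16 (p=3%, q=45%, r=4).
- Planned repeat, 1+q(r−1): 1.25 to 2.35.
- Both countries restricted: 1.00, by construction.

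The planned repeat thus moves further from the true value of 1.

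**4. What stays in on the New Zealand side.** Among under-5s in 2020, the rate in the *other* group is 0.33/(1−q) of the all-children rate: 0.44 at q=25% and 0.60 at q=45%. Keeping Māori and Pacific children makes the New Zealand rate about 1.7–2.3 times that of the group closest in definition to non-Indigenous Australians.

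**5. Missing Indigenous status.** Cases without status count as non-Indigenous, while the population denominator is assumed unaffected. If a fraction m of Indigenous cases lacks status and s = pr/(1−p+pr) is the Indigenous share of cases, the Australian rate is multiplied by (1−s+ms)/(1−p). With p=6% and r=2, s = 0.12/1.06 = 0.113.
- m=0: 0.943, so the ratio is multiplied by 1.06.
- m=10%: 0.955, so 1.05.
- m=50%: 1.004, so just under 1.00.

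In this example the rise disappears at m = 1 − 1.06/2 = 47%. With r=4 it disappears at m = 1 − 1.18/4 = 71%.

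**The case against.** The strongest reply is that the asymmetry is deliberate. The reason for exclusion is extra dosing, and the protocol says Māori and Pacific people get no additional doses. They receive the New Zealand programme under study, so the dosing reason gives no ground to drop them. This stands, and it is why the exclusion should be kept. It does not make the two remaining populations comparable in baseline risk.

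A second reply is that the comparison is almost there already. The ethnic step produces an Australian non-Indigenous rate and a New Zealand *other* rate, and repeating all analyses would repeat that step. The strata do exist, which makes the remedy cheap. But the text states the contrasts within each country, with "Māori and Pacific vs other for New Zealand" on one side, and never pairs the two lower-risk groups.

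Third, most of the ethnic-mix distortion is already in the unrestricted comparison: 1.18–2.16 in the scenario above, against 1.25–2.35 after restriction. That is true, and the study calls itself descriptive, with no robustness criterion. The point is therefore about what the repeat can show, not about the whole study.

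Fourth, a matched contrast is not truly matched. Any Pacific people in Australia stay in the non-Indigenous group, since the Australian definition covers only Aboriginal and Torres Strait Islander people, and cases with missing status stay there too. This also stands and must be stated as a limit.

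A reader might infer that matching both sides would reverse the direction of the 2019 ratio. The documents do not support that: it would apply an under-5 case share from one year to an all-age ratio, and the protocol gives neither under-5 rates nor an all-age Māori and Pacific case share.

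**Conclusion.** The concern holds for IPD rates. As written, the sensitivity analysis mixes the extra-dose question with a one-sided change in baseline risk. It multiplies the NZ:Australia ratio by about 1.03–1.35 for p of 3–7% and r of 2–6, or up to 1.40 at p of 8%. The direction rests on the protocol's statement of higher Indigenous burden, taken to apply to Australian children; the size rests wholly on the assumed p and r. Missing status shrinks the shift and, if about half of Indigenous cases lacked it and r were only 2, could cancel it.

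Two stronger readings are tempting. One is that every result of the repeat shifts towards New Zealand. That cannot be shown for the proportion of cases with serotype 19A, because the protocol gives no ethnic breakdown of serotypes in Australia. The other is that the whole shift is risk mix and none of it dosing. The exclusion removes the extra-dose recipients as well, so the repeat cannot separate the two.

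**What to change.** Keep the dosing-based exclusion. Add one sentence to Data analysis: the sensitivity analysis will also compare non-Indigenous children in Australia with non-Māori, non-Pacific children in New Zealand, and any reading about the vaccine programmes will rest on this contrast, not on the version restricted in Australia alone. Report both, and say that the one-sided version changes ethnic risk mix as well as dosing.

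The cost is one more set of rate ratios from strata already planned. State two downsides. New Zealand intervals will be wider: with about one third of under-5 cases left (33% on the 2020 figures), the standard error of the log rate for that group grows by roughly 1/√0.33 = 1.74. Matching will be imperfect, because Pacific people in Australia and cases with missing Indigenous status remain in the Australian group; reporting the number of cases with missing status would let readers judge the latter.

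### Counting Australian cases of unknown Indigenous status as non-Indigenous understates the Indigenous IPD rate and the Indigenous versus non-Indigenous contrast if any of those cases are Indigenous

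*Protocol*

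**What the plan says.** The data analysis paragraph of the Protocol (Methods) plans, for Australia, a comparison by status: "Indigenous (Aboriginal and Torres strait islander) versus non-Indigenous for Australia". It also plans a restricted repeat: "In a sensitivity analysis, we will repeat all the analyses only including non-Indigenous children in Australia because Indigenous children receive additional doses of PCV". It then settles unknown status in one sentence: "Cases with missing indigenous status were counted as non-indigenous". The protocol uses the word Indigenous for the Australian strata and Māori, Pacific and other for the New Zealand strata, so I read this rule as Australian.

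Numerators are notifications from the national surveillance systems. For denominators, the investigators will "merge those with census data that will be derived from Australian Bureau of Statistics and Statistics New Zealand". The protocol describes no adjustment linking the two. It gives no reason for the rule, no missing share and no alternative handling.

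Under Relevance to Māori health, the protocol states: "Indigenous populations in New Zealand and Australia, along with Pacific peoples have a much higher burden of disease for IPD". Ethnicity is named as a focus in the study objective.

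**The concern.** The rule is a single imputation to one category, and it is applied to the numerator only. Each Indigenous case without recorded status is removed from the Indigenous count and added to the non-Indigenous count, while the person remains in the Indigenous population. One rate is pushed down, the other up, and the contrast between them shrinks.

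This error is systematic, so more years or more cases do not reduce it. It falls on a group whose burden the protocol specifically sets out to measure. The one sensitivity analysis named does not test the rule, because it uses the same classification.

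**Working it through.** **The plan's own figures.** The only rates given are the overall 2019 rates per 100,000 for Australia and New Zealand, which "are on average 8.4 (95%CI 8.1-8.8), and 9.9 (95%CI 9.1-10.8), respectively". Case counts and populations are not stated. They can be approximated from the interval width, using SE = width/(2 × 1.96) and events = (rate/SE)².

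- Australia: SE = 0.7/3.92 = 0.179; events = (8.4/0.179)² ≈ 2,213, in about 26.3 million people.
- New Zealand: SE = 1.7/3.92 = 0.434; events = (9.9/0.434)² ≈ 521, in about 5.3 million people.

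The figures are coherent with Poisson counts but say nothing about missing status.

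**Direction.** Let E_I and E_N be the true Indigenous and non-Indigenous case counts, and N_I and N_N the populations. Let M be the number of cases with unknown status, of which a share q is Indigenous. Under the rule:

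- Indigenous rate = (E_I − qM)/N_I
- non-Indigenous rate = (E_N + qM)/N_N

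For any q > 0 the first is too low, the second too high, and their ratio too low. For q = 0 there is no bias. The sum of cases is unchanged, so the overall Australian rate does not move.

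**Size if status is missing at random.** Let p be the Indigenous share of all cases and m the missing share. Then qM = m·E_I, and:

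- Indigenous rate is multiplied by 1 − m
- non-Indigenous rate is multiplied by 1 + m·p/(1 − p)
- rate ratio is multiplied by (1 − m)/(1 + m·p/(1 − p))

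Example with p = 20%, m = 10%: 0.90/(1 + 0.10 × 0.25) = 0.90/1.025 = 0.878.

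Both p and m are assumed; neither is in the protocol.

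| p | m | Indigenous rate | non-Indigenous rate | rate ratio multiplied by |
|---|---|---|---|---|
| 10% | 5% | −5% | +0.6% | 0.945 |
| 20% | 5% | −5% | +1.25% | 0.938 |
| 30% | 5% | −5% | +2.1% | 0.930 |
| 10% | 10% | −10% | +1.1% | 0.890 |
| 20% | 10% | −10% | +2.5% | 0.878 |
| 30% | 10% | −10% | +4.3% | 0.863 |
| 20% | 20% | −20% | +5.0% | 0.762 |

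**Check by another route.** Assume a 3% Indigenous population share, a true ratio of 4 and m = 10%, anchored to the stated 8.4. The true non-Indigenous rate is 8.4/(0.97 + 0.03 × 4) = 7.71, and the Indigenous rate is 30.8. Here p = 0.12/1.09 = 11%. The rule gives 27.7 and 7.80, so a ratio of 4.0 is reported as 3.56, a factor of 0.89.

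**Not missing at random.** Only the missing share among Indigenous cases enters the algebra. If status is recorded more completely for Indigenous cases, replace m by that smaller share and the bias shrinks; if less completely, it grows.

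**Alternatives, at p = 20% and m = 10%, per unit of all cases.** Known cases are 0.18 Indigenous and 0.72 non-Indigenous, with 0.10 unknown.

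- Proportional allocation: 0.18 + 0.10 × 0.18/0.90 = 0.20, the true share.
- All unknown counted as Indigenous: (0.18 + 0.10)/0.20 = 1.4 times the true Indigenous rate.
- Dropping unknowns: both rates are 10% too low, so exclusion is not a cure.

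**The case against.** The strongest case against is that nothing shows the problem is material. Neither m nor p is in the protocol; at m = 1% to 2% the ratio moves by only about 1% to 3%. The bias is also conditional: it vanishes if no unknown-status case is Indigenous. Both statements are right. They limit what can be said about size, but they do not support the rule, since the protocol offers no reason to expect few unknowns and itself reports a much higher Indigenous burden.

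A reader might infer several stronger things that the protocol does not support:

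- *The overall country comparison is biased.* It is not. Overall rates, the serotype 19A proportion by country and the all-ethnicity age analyses do not use Indigenous status.
- *The non-Indigenous sensitivity analysis is seriously distorted.* The direction is upward, but the size is about +0.6% to +2.1% at m = 5% and +1.1% to +4.3% at m = 10%. The stated interval for the whole Australian population already spans −3.6% to +4.8% around 8.4, and a subset of children will have a wider one.
- *The rule creates false time trends or false differences in inequity between the countries.* The methods specify neither an ethnicity-by-year trend nor a between-country contrast of ethnic ratios, and they name no rate ratio. The ratio is used here only to measure the distortion of the stratified comparison.
- *Multiple imputation is required.* The ethics section says the surveillance data are aggregated, so case-level imputation may not be possible.

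It is also fair to say that missing-data reporting and the handling of unknown ethnicity in New Zealand may sit in an analysis plan not shown here. The point therefore rests on the rule that the protocol does fix.

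**Conclusion.** The point holds for the Australian stratified analysis. The rule lowers the Indigenous rate and narrows the Indigenous versus non-Indigenous contrast whenever some unknown-status cases are Indigenous, which is likely but not demonstrated. With status missing at random, the Indigenous rate is low by m, and for assumed p of 10% to 30% the ratio is multiplied by about 0.93 to 0.95 at m = 5% and 0.86 to 0.89 at m = 10%.

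For scale, if p were 20% of the roughly 2,213 Australian cases back-calculated for 2019, there would be about 443 Indigenous cases, with a 95% half-width near 1.96/√443 = 9.3%. A 10% understatement would then be about as large as one year's sampling error.

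The sensitivity analysis is affected only slightly, through a marginally high rate and the retention of some Indigenous children whose extra doses are the reason for the restriction. The rule should be changed, but it does not threaten the main country comparison.

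**What to change.** In the stratified analysis, replace the single rule with proportional allocation of unknown-status cases within the cells available: age group and year, and jurisdiction if it is supplied. Report the missing share alongside. Keep the present rule as one bound and count all unknowns as Indigenous for the other. Repeat the non-Indigenous sensitivity analysis under the allocation.

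Allocation needs only case counts by recorded status (Indigenous, non-Indigenous, unknown) in each cell, so it is compatible with aggregated data. If jurisdiction tables would require a new request, age group and year are enough to start.

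The cost is a little more analysis. Allocation assumes that status is missing at random within cells. The bounds make that assumption visible, although the upper one can be wide, as the 1.4 above shows. If the bounds turn out narrow, robustness has been shown.
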